## Abstract

**Background:**

Night shift work-related disturbed biological rhythm and insufficient sleep affect the functioning of brain activity and thus impair cognitive performance and mood state, which potentially leads to negative and even devastating results for both individuals and patients. A virtual reality (VR)-based restorative environment has shown to be an effective new technique to reduce stress and improve cognitive performance, but little is known about its mechanism of improving neuronal activity and connectivity.

**Methods:**

This is a randomized, controlled, single-center clinical trial. A total of 140 medical staff will be enrolled and randomized in a 1:1 allocation to either the VR immersion group (intervention group) or the control group. In the morning after the night shift, the participants in the intervention group will watch 360° panoramic videos of immersive VR natural restorative environments for 10 min, while the participants in the control group will just rest for 10 min. Assessments of abbreviated Profile of Mood States Questionnaire (POMS) and verbal fluency task (VFT) performances, as well as oxygenated hemoglobin (oxy-Hb) and deoxygenated hemoglobin (deoxy-Hb) and total hemoglobin concentration acquired by functional near-infrared spectroscopy (fNIRS) will be performed at baseline (day work), the morning after night shift but before the intervention (previous) and after intervention (post). Data collected after a night shift will be compared to baseline performance as well as between the two groups.

**Discussion:**

This trial will investigate the effects of the night shift and VR-based restorative environment intervention on mood, cognitive performance, and neuronal activity and connectivity. A positive result in this trial could encourage hospitals to apply VR technology to reduce physical and mental dysfunction during of night shifts among medical staff in every department. Furthermore, the findings from this study will contribute to understanding the underlying neuromodulation mechanisms of how restorative environments influence mood and cognition.

**Trial registration:**

Chinese Clinical Trial Registry ChiCTR2200064769. Registered on 17 October 2022.

## Introduction

### Background and rationale {6a}

Medical staff often work night shifts to ensure the health of patients. Since night shift work is associated with a disturbed biological rhythm and insufficient sleep, this often leads to psychosomatic stress, such as depression, cognitive impairment, burnout, cardiac autonomic dysregulation, and increased risk of work errors [1–5]. The COVID-19 pandemic has exacerbated stress and burnout among medical staff. Multiple studies have confirmed that night shift work has a passive effect on advanced cognitive function, including working memory capacity, speed of processing information, perceptual reasoning, and cognitive flexibility [2]. The prefrontal lobe is known to play an important role in emotional control and higher cognitive functions. Functional neuroimaging studies have shown that night duty leads to reduced brain activity and decreased brain functional connectivity density of the frontal cortex [3, 6, 7]. Therefore, an increasing number of studies have focused on the damaging effects of night shifts on medical staff and the development of effective interventions that can relieve stress, which would be valuable in enhancing patient safety and protecting the health of medical staff.

Restorative environments (mainly natural environments) have been beneficial for restoring attention, reducing stress, and improving physical and mental health, and could potentially meet the physical and mental needs of medical staff [8, 9]. Recently, VR technology has shown great potential in the field of mental health, and the combination of restorative environments and VR technology has been effective for emotional and cognitive recovery [10–12]. An EEG study showed that the VR restorative scene experience could activate the frontal lobe, suggesting an important mechanism that could be conducive to cognitive and emotional recovery [12]. Furthermore, VR technology had been used to decrease the physical and mental workload of anesthesiologists on night shifts and reduce the stress response and cognitive load of inpatient oncology nurses [13, 14]. Therefore, the VR restorative environment may be an effective intervention measure to reduce night shift stress, which would be of great significance in improving medical safety and protecting the health of medical staff. However, there are no studies yet that have investigated the neural mechanism of the regulatory effect of the VR restorative environment on frontal lobe activity after night shift work.

Previously, fNIRS studies have shown decreased prefrontal cortex (PFC) activity in night duty physicians [6]. In addition, night shift sleep deprivation impairs performance on cognitive tasks, including VFT, which are thought to rely on PFC involvement and are less activated by cognitive tasks in sleep deprivation (night shift) than in rested subjects (day shift) [7]. However, how this abnormal activation can be regulated by VR has not been reported. This protocol describes the implementation of watching 10 min of a VR restorative environment among medical staff after a night shift, and fNIRS is used to measure the changes in frontal lobe activity before and after the intervention.

### Objectives {7}

This trial will investigate the effects of the night shift and VR-based restorative environment intervention on mood, cognitive performance, neuronal activity, and brain functional connectivity. A positive result in this trial could encourage hospitals to apply VR technology to reduce physical and mental dysfunction during night shifts among medical staff in every department. Furthermore, the findings from this study could contribute to understanding the underlying neuromodulation mechanisms of how restorative environments influence mood and cognition.

### Trial design {8}

The study is a parallel two-group randomized controlled trial comparing the mood, cognitive performance, and brain activation of medical staff who undergo and do not undergo VR immersion after a night shift. In addition, data collected from a day shift are assessed and serve as a normal baseline. A total of 140 volunteers (including physicians and nurses) will be randomized in a 1:1 allocation to the intervention group and the control group by the block randomization method. fNIRS and abbreviated POMS assessments will be used at three time points collected throughout the study to assess how night shift and VR restorative environment immersion affect frontal cortex activity and mood in physicians and nurses [15, 16]. The collection time points are as follows: the first is collected during the day shift which is at least 3 days after the last night shift, and the last two are collected in the morning after the night shift (at 8:00–9:00 am) before and after VR intervention/rest. The interval between day shift and night shift assessments is at least 14 days. The intervention group will undergo immersion relaxation by watching their favorite VR restorative environment video for 10 min at 8:30 am after the night shift, while the control group will rest quietly for 10 min awake. The timeline design of the study is presented in Fig. 1.

**Fig. 1 Fig1:**
[figure not shown]
Expected trial plan. Not included in the diagram are excluded participants who may stop participation at any time for various reasons. The intervention is 10 min.

The primary outcomes of the study will be the different cerebral oxygenation levels assessed during VFT performances using fNIRS, to evaluate the alterations in regional activity and functional brain network connectivity in the PFC. Secondary outcomes will be the abbreviated POMS scores at all the recorded time points [16].

## Methods: participants, interventions, and outcomes

### Study setting {9}

The study will be conducted in the First Affiliated Hospital of Dalian Medical University, a large comprehensive hospital in Dalian, China. This is a teaching hospital, including more than 90 nurses and more than 100 physicians aged from 20 to 45 in the Department of Neurology. The night shift is from 17:00 to 8:00 of the next day.

### Eligibility criteria {10}

Potential participants will be recruited from the Neurology Department of the First Affiliated Hospital of Dalian Medical University. Only individuals who meet the inclusion criteria will be invited to participate in the study.

Eligibility criteria include the following:Aged 20–45 years oldRegular shift work for more than 1 yearRight-handed

Exclusion criteria include the following:History of neurological diseases, head trauma, or surgeryUsing sedatives or stimulantsOther reasons for ineligibility

### Additional consent provisions for collection and use of participant data and biological specimens {26b}

On the consent form, participants are asked if their data can be used even if they choose to withdraw from the trial. Participants are also asked for permission of the research team to share relevant data with personnel from regulatory authorities, where relevant. The trial does not involve the collection of biological specimens.

## Interventions

### Explanation for the choice of comparators {6b}

To assess the damaging effects of the night shift, the brain activity, VFT performance, and mood state outcomes of the day shift will be compared with those after the night shift. To assess the beneficial effects of VR-based restorative environment intervention on mood, cognitive performance, and brain activity, those outcomes will be compared among pre- and post-VR intervention and simple relaxation.

### Intervention description {11a}

The intervention time point is approximately 8:30 am after the night shift. All participants will complete the fNIRS and abbreviated POMS first, which takes approximately 20 min. Participants in the intervention group will recline comfortably on a sofa, wearing a VR glass loaded with an intelligent VR psychosomatic interactive training system (Ruixin, Ruihai Yinuo Intelligent Technology Co., Ltd., China) and watch 360° panoramic videos of the immersive VR natural restorative environment selected according to their preferences to relax themselves in the resting room. The intervention time will be 10 min. After the intervention, all participants will complete the fNIRS and abbreviated POMS again. Participants in the control group also recline comfortably on a sofa but only rest for 10 min without VR immersion. After relaxation, all participants will complete the fNIRS and abbreviated POMS again.

### Criteria for discontinuing or modifying allocated interventions {11b}

Participants may quit at any time due to various reasons including failure to meet inclusion criteria or inability to continue VR intervention.

### Strategies to improve adherence to interventions {11c}

Not applicable because it is a one-time intervention.

### Relevant concomitant care permitted or prohibited during the trial {11d}

Not applicable because all participants are healthy.

### Provisions for posttrial care {30}

Not applicable to study; no harm is anticipated from this study as the equipment used poses little risks.

### Outcomes {12}

The primary outcomes are the oxy-Hb and deoxy-Hb concentration of brain cortex acquired by fNIRS and VFT performances at three assessment time points (baseline, after the night shift before VR immersion, after VR immersion), to evaluate the alterations of in regional brain activity and functional brain network connectivity in the PFC. The secondary outcomes will be the abbreviated POMS scores at all the recorded time points.

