### Sample size {14}

In this protocol, a total of 140 participants (70 participants in two groups) will be recruited over an 18-month period. We aim to recruit an even distribution of age and gender to maximize statistical significance. The primary outcomes are the oxy-Hb and deoxy-Hb concentrations of the brain cortex acquired by fNIRS at baseline, after the night shift before VR immersion, and after VR immersion (or after rest). We assumed that the VR intervention group would show better recovery of PFC function than the non-intervention group. Because there are no pilot studies or previous studies, the sample size was calculated using G*Power software (downloadable from: https://download.cnet.com/G-Power/3000-2054_4-10647044.html), with 80% power, 2-sided 5% significance level, and a moderate effect size *d*=0.5. We assume that the mean of the two groups are the same. This sample size of 140 participants also allows for 10% loss to follow-up. Durán-Gómez N et al.’s study was used to estimate the baseline averages of oxy-Hb changes[7]. However, there are notable inherent differences between this protocol and Durán-Gómez N et al.’s study because the latter only described oxy-Hb changes before and after a night shift without other intervention [7].

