#### fNIRS

The fNIRS assessment will be employed to examine the cortical neural activity changes from the night shift and VR intervention. A multichannel near-infrared brain function imaging device (NirSmart, Danyang Huichuang Medical Equipment Co., Ltd., China) will be used to record changes of oxy-Hb and deoxy-Hb, and the emission light sources will be 730 nm and 850 nm, respectively. There are 23 emitters and 15 detectors to form 47 effective channels. The distance between channels is 3 cm, and the sampling rate of all channels is ≥11 Hz. The probe set will be placed on the scalp corresponding to the PFC, premotor and supplementary motor cortex, motor cortex, and sensory cortex, according to the international 10–20 system for electroencephalogram. The Cz and Fz positions from the 10–20 system are first identified. Detector D2 corresponds to the Fpz point. The midpoint of the connecting line between emitter S13 and emitter S14 corresponds to the Cz point (Fig. 3).

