#### fNIRS data

The raw fNIRS data will be bandpass filtered first and further processed to remove noise and drift. Neuroactivity in various regions of interest will be analyzed by constructing a general linear model for each subject then estimating parameters and obtaining contrast values of the oxy-Hb and deoxy-Hb signals. The contrast values will be averaged within groups and a group analysis will be performed using a *t* test. The averaged signal levels between two groups and between different assessment time points will be compared to determine the intervention effect.

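### The primary outcome is stated inconsistently and in the plural, with no deciding test, while the sample size allows for one comparison at an unsplit 5%

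*Protocol article*

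**What the plan says.** The protocol article defines the primary outcome in three places.

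- **Trial design {8}**, in the text after Fig. 1, names cerebral oxygenation levels recorded during the VFT. Their purpose is "to evaluate the alterations in regional activity and functional brain network connectivity in the PFC".
- **Outcomes {12}**: "The primary outcomes are the oxy-Hb and deoxy-Hb concentration of brain cortex acquired by fNIRS and VFT performances at three assessment time points". Only the abbreviated POMS is listed as secondary.
- **Sample size {14}**: "The primary outcomes are the oxy-Hb and deoxy-Hb concentrations of the brain cortex acquired by fNIRS at baseline", followed by the two later time points. No VFT score appears.

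On analysis, the fNIRS data section says: "Neuroactivity in various regions of interest will be analyzed by constructing a general linear model for each subject". It obtains contrast values for both signals and compares groups by t test. It also compares average signal levels both across arms and across visits, as its way of establishing whether the intervention worked. The VFT score has its own t test in the preceding section.

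The sample size is calculated "with 80% power, 2-sided 5% significance level, and a moderate effect size" of d=0.5. That is the only significance level in the document. The effect size is not tied to a signal, region, time point or contrast.

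**The concern.** The three definitions do not agree. The wording in Outcomes {12} can be read with the VFT score as a third primary outcome, or with the VFT as merely the task during which the signals are recorded. On the first reading it contradicts Sample size {14}. On the second, the VFT score, which has its own definition and its own test, is neither primary nor secondary.

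Even the shortest list is plural: two signals at three time points. The fNIRS analysis adds several regions, and it treats changes over time as evidence of an intervention effect alongside differences between arms. Nothing says which comparison decides the trial, or whether one success is enough or all are needed. What counts as a positive result could therefore be settled after the data are seen. The Objectives say that such a result could encourage hospitals to take up VR, so the deciding test should be fixed in advance.

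**Working it through.** **Inputs.** From Sample size {14}: 80% power, two-sided 5%, d=0.5, 10% loss, 140 in total. From Trial design {8}: 1:1 allocation. Assumed, because the document gives no figure: correlations of 0 to 0.8 between test statistics, and a true effect of d=0.5 on each outcome for the power figures.

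**1. The plan's own figure.** Normal approximation, per arm: n = 2(1.960 + 0.842)²/0.5² = 62.8, so 63. With 10% loss, 63/0.9 = 70 per arm, 140 in total. This reproduces exactly. The exact t test asks for 64 per arm (128/0.9 = 142.2 in total), which is close. With 63 analysed per arm, power for one test is 80.1% (normal) or 79.5% (noncentral t). So 140 is right for one comparison.

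**2. Any one of k unadjusted 5% tests counts.** For independent tests, the chance of at least one false positive is 1 − 0.95^k. Correlated cases come from simulating equicorrelated normal statistics (400,000 draws).

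| Primary list (one region, one contrast) | Correlation 0 | 0.5 | 0.8 |
|---|---|---|---|
| Two signals (k=2) | 9.8% | 9.1% | 7.8% |
| Two signals and VFT (k=3) | 14.3% | 12.4% | 9.8% |

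Under this rule the chance of a positive result when d=0.5 holds throughout is above 80% (87-96% for k=2, 90-99% for k=3). What fails is the 5% error rate, not the power.

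**3. Alpha split by Bonferroni.** Noncentral t, 63 per arm:

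- k=2, alpha 0.025: power 70.4%. Restoring 80% needs 78 per arm, and 78/0.9 rounds up to 87, so 174 in total.
- k=3, alpha 0.0167: power 64.8%. Restoring 80% needs 86 per arm, and 86/0.9 rounds up to 96, so 192 in total.

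**4. All k must be significant at 5%.** The expected value of each test statistic is 0.5 × √(63/2) = 2.81, so each test alone has 80.1% power. If independent, joint power is 0.801² = 64% for k=2 and about 52% for k=3 by simulation. At correlation 0.8 it is 73% and 69%.

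**5. Further regions or contrasts.** The number of regions is not given, so any figure here is an assumption. As an illustration, six tests (say two signals in three prefrontal regions) would give 26.5% if independent, 20.7% at correlation 0.5 and 13.8% at 0.8.

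**The case against.** The strongest reply is that region selection, multiplicity rules and success criteria are commonly left to an analysis plan or full protocol, and neither is shown. That stands: the lack of an adjustment rule is not the finding, and testing each outcome at 5% is an inference from the one level quoted in Sample size {14}. But a later plan could not follow all three definitions of the primary outcome at once, and splitting alpha in it would lower the power stated here. The Discussion also calls the results preliminary and in need of larger confirmation, which softens the consequence.

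Several stronger readings are tempting, and the document does not support them.

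- **Total haemoglobin as another primary.** The abstract lists it among the assessments and does not call it primary.
- **Connectivity as a separate primary.** Trial design {8} and Outcomes {12} share the same purpose clause. Connectivity is what the outcomes should shed light on, and no endpoint or test for it is listed.
- **A very large family of tests.** The fNIRS section says "There are 23 emitters and 15 detectors to form 47 effective channels", and 47 channels times two signals makes 94 tests, with a 99% chance of a false positive if independent. But that sentence describes the equipment; the analysis is by region of interest. Likewise, four probe areas times two signals plus VFT (nine tests, 37% if independent) assumes a family that the outcome definitions, which point to the prefrontal cortex, do not state.
- **A false positive is likely.** For the stated lists the chance is about two to three times nominal, not more likely than not.
- **The 80% power is wrong.** It holds for one test and fails only if alpha is split or every outcome must succeed.

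**Conclusion.** The point holds. The primary outcome is defined in three ways that do not agree, no deciding signal, region, time point or contrast is named, and the sample size provides for a single test. For the lists as stated, either the error rate rises to about 8-10% (two signals) or 10-14% (three outcomes), or power falls below the planned 80%. The fall is to 70% or 65% with Bonferroni, and to 64-73% or 52-69% if all must succeed. No success rule holds both 5% and 80% for these lists over the correlations examined.

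These figures rest on the assumed correlations, one region and one contrast per outcome, d=0.5 on every outcome and 63 analysed per arm. More regions or within-arm contrasts would raise the error rate by an amount that the document does not allow one to fix. The sample-size arithmetic itself is sound.

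**What to change.** In Trial design {8}, Outcomes {12} and Sample size {14}, name the same single primary outcome: one signal, in the prefrontal cortex, at one time point, compared between arms. One suitable form is the between-arm difference at T3 in the prefrontal oxy-Hb task contrast, adjusted for T2. The choice of signal is the investigators' to make. Make the other signal, the VFT word count, connectivity, other regions, and the day-versus-night and within-arm comparisons secondary or exploratory. Reword the fNIRS data section so that only the between-arm comparison decides the intervention effect.

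The 140 participants and the 80% power then stand. The cost is wording, plus a registry update made before unblinding, and fewer results can be called primary.

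Alternatively, keep several primaries, state the success rule, split alpha and restate the power. Holding 80% with Bonferroni would need about 174 participants for two primaries or 192 for three.

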### Participant timeline {13}

Figure 1 graphically shows the participant timeline.

Figure 2 illustrates the standard protocol.

**Fig. 2 Fig2:**
[figure not shown]
Standard Protocol Items: Recommendation for Interventional Trials (SPIRIT). *VR* Virtual reality, *VFT* Verbal fluency test, *fNIRS* Functional near-infrared spectroscopy, *POMS* Profile of Mood States Questionnaire.

### Sample size {14}

In this protocol, a total of 140 participants (70 participants in two groups) will be recruited over an 18-month period. We aim to recruit an even distribution of age and gender to maximize statistical significance. The primary outcomes are the oxy-Hb and deoxy-Hb concentrations of the brain cortex acquired by fNIRS at baseline, after the night shift before VR immersion, and after VR immersion (or after rest). We assumed that the VR intervention group would show better recovery of PFC function than the non-intervention group. Because there are no pilot studies or previous studies, the sample size was calculated using G*Power software (downloadable from: https://download.cnet.com/G-Power/3000-2054_4-10647044.html), with 80% power, 2-sided 5% significance level, and a moderate effect size *d*=0.5. We assume that the mean of the two groups are the same. This sample size of 140 participants also allows for 10% loss to follow-up. Durán-Gómez N et al.’s study was used to estimate the baseline averages of oxy-Hb changes[7]. However, there are notable inherent differences between this protocol and Durán-Gómez N et al.’s study because the latter only described oxy-Hb changes before and after a night shift without other intervention [7].

